**Methods/Design:**

*ADDITION-Plus *is an explanatory randomised controlled trial of a facilitator-led, theory-based behaviour change intervention tailored to individuals with recently diagnosed type 2 diabetes. 34 practices in the East Anglia region participated. 478 patients with diabetes were individually randomised to receive **(i) **intensive treatment alone (n = 239), or **(ii) **intensive treatment plus the facilitator-led individual behaviour change intervention (n = 239). Facilitators taught patients key skills to facilitate change and maintenance of key behaviours (physical activity, dietary change, medication adherence and smoking), including goal setting, action planning, self-monitoring and building habits. The intervention was delivered over one year at the participant's surgery and included a one-hour introductory meeting followed by six 30-minute meetings and four brief telephone calls. Primary endpoints are physical activity energy expenditure (assessed by individually calibrated heart rate monitoring and movement sensing), change in objectively measured dietary intake (plasma vitamin C), medication adherence (plasma drug levels), and smoking status (plasma cotinine levels) at one year. We will undertake an intention-to-treat analysis of the effect of the intervention on these measures, an assessment of cost-effectiveness, and analyse predictors of behaviour change in the cohort.

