### Statistical analysis

The additional benefit of the facilitator-led behaviour change intervention on objective measures of physical activity level, medication adherence, and change from baseline in plasma vitamin C and smoking status will be assessed using an intention to treat analysis comparing the intervention and comparison groups, using linear regression for continuous outcomes and a comparison of proportions for binary outcomes. Continuous outcomes will be analysed with adjustment for the baseline value of the outcome, where this has been measured, in order to improve precision. Those participants missing the baseline value will remain included in the analysis by using the missing indicator method, which is valid for pre-randomisation measures in trials [69]. Due to the large number of stratifier categories, there will be no adjustment for stratifiers in order to ensure that estimation of intervention effects is stable. The modelled ten-year cardiovascular risk will be log transformed before analysis and computed for those with and without a history of previous CVD events. The primary intention to treat analysis will be supported by per protocol analyses of primary outcomes, where the per protocol population is defined to be those participants attending the introductory and initial three core intervention sessions. The impact of missing primary outcome data will be examined within sensitivity analyses using the multiple imputation method of Rubin [70]. This will involve fitting an imputation model from the observed data, from which missing data will be imputed under two opposing scenarios. In the first scenario it is assumed that the same full intervention-minus-comparison effect applies amongst participants with missing data as has been observed amongst their counterparts with observed data. In the second scenario it is assumed that the intervention-minus-comparison effect is zero for participants with missing data. Ten complete datasets will be imputed, as recommended, to incorporate the uncertainty in the residuals and parameter estimates of the imputation model. Subgroup analyses will be confined to the comparison of intervention effects on primary outcomes by the route of diagnosis (screen-detected versus already-diagnosed).

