### Sample size

The trial was designed within the main *ADDITION-Cambridge *trial. It was anticipated that 500 patients would participate in the *ADDITION-Plus *trial and that 200 individuals per group would be available with follow-up data. With these numbers, there is 80% power at the 5% level of significance level to detect the following relevant differences between arms in primary outcomes:

Physical activity:

A 0.017 kJ/kg/min difference in PAEE. This is based on a standard deviation of 0.058 at baseline in the *ProActive *trial dataset [72] with mean 0.078. A 0.017 absolute difference represents a 22% relative difference in mean energy expenditure between groups.

Diet:

A 5.5 umol/l difference in plasma vitamin C (control group mean 53, SD 19, EPIC study [73]). Adjustment for baseline level in the analysis allows a finer difference of 4.0 umol/l to be detected between arms (EPIC test-rest correlation of 0.67).

Medication adherence:

A 10% absolute difference in the proportion of low adherers to hypoglycaemic medications (control group 18%, Supported Adherence to Medication pilot study [51]).

Smoking:

A 9.5% absolute difference in the proportion smoking (control group 17.9%).

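### Ten imputations give valid missing-data sensitivity results, but borderline ones are not well reproducible; about 100 per scenario would fix this at almost no cost (optional improvement)

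*Protocol article*

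**What the plan says.** The Statistical analysis section of the protocol article gives multiple imputation a supporting role: "The impact of missing primary outcome data will be examined within sensitivity analyses using the multiple imputation method of Rubin". There are two scenarios. In the first, "it is assumed that the same full intervention-minus-comparison effect applies amongst participants with missing data" as was seen in those with data. In the second, "it is assumed that the intervention-minus-comparison effect is zero for participants with missing data". The number of imputations is then fixed: "Ten complete datasets will be imputed, as recommended". The article does not tie this number to the amount of missing data or to a tolerance for Monte Carlo error, and it attaches no significance rule to the imputed results.

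The amount of missing data to expect follows from two other places. The Sample size section anticipated that "500 patients would participate in the" trial and that "200 individuals per group would be available with follow-up data". The abstract reports that "478 patients with diabetes were individually randomised", 239 per arm.

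**The concern.** Ten imputations are usually justified by efficiency: the pooled estimate is almost as precise as with an unlimited number. Reproducibility is a separate question. Each run draws random values, so a second run with another seed gives a somewhat different estimate, standard error and p-value.

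Two scenarios on four primary outcomes give eight sensitivity results. Each will be read against the primary analysis, and the two scenarios against each other. If seed noise is appreciable relative to the standard error, whether a borderline result agrees with the primary analysis is partly an accident of the seed. The scenario contrast, which is the purpose of the exercise, is blurred as well.

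**Working it through.** **Inputs**
- Number of imputations: m = 10 (Statistical analysis).
- Planned missing fraction: (500 − 400)/500 = 20% (Sample size), or (478 − 400)/478 = 16.3% if 400 of those actually randomised are followed up.
- Fraction of missing information (FMI): not in the documents. It is assumed about equal to the missing fraction, 0.163–0.20; a wider range is shown below.

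The article gives no derivation for ten, so there is no figure to reproduce.

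**Efficiency.** Relative efficiency = 1/(1 + FMI/m).
- 1/(1 + 0.0163) = 98.4%
- 1/(1 + 0.020) = 98.0%

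Efficiency is not a problem.

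**Seed noise.** Monte Carlo SE divided by the estimate's SE = √(FMI/m).

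| FMI | m = 10 | m = 100 |
|---|---|---|
| 0.163 | 0.128 | 0.040 |
| 0.20 | 0.141 | 0.045 |

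Over an assumed FMI range of 0.05–0.40, the m = 10 figure runs from 0.071 to 0.200.

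**Effect on a p-value of 0.05.** The 95% range of z across seeds is 1.96 ± 1.96 × √(FMI/m).
- FMI 0.163, m = 10: z from 1.71 to 2.21, p from 0.087 down to 0.027.
- FMI 0.20, m = 10: z from 1.68 to 2.24, p from 0.092 down to 0.025.
- FMI 0.163, m = 100: z from 1.88 to 2.04, p from 0.060 down to 0.041.
- FMI 0.20, m = 100: z from 1.87 to 2.05, p from 0.061 down to 0.041.

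**Simulation check.** One incomplete two-arm dataset with a normal outcome was held fixed and re-imputed with 4,000 seeds, pooling by Rubin's rules with small-sample degrees of freedom. Missing data were 39 of 239 or 50 of 250 per arm. The ranges are slightly wider than the formula gives, because the estimated standard error also varies by seed. For a many-imputation p of 0.05 and m = 10, the 95% ranges were:

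| Missing | Scenario 1 (full effect) | Scenario 2 (zero effect) |
|---|---|---|
| 16.3% | 0.026–0.099 | 0.027–0.095 |
| 20% | 0.023–0.110 | 0.024–0.103 |

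Share of seeds on the other side of 0.05 at m = 10:
- many-imputation p of 0.03: 9–15%
- many-imputation p of 0.07: 11–16%
- many-imputation p of 0.01 or 0.10: at most about 2%

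In scenario 1 with 20% missing, going to m = 100 narrows the range around p = 0.05 to 0.039–0.064. The crossing share falls from 15% to about 0% at p = 0.03, and from 16% to 0.3% at p = 0.07.

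**Noise against the scenario contrast.** With equal loss in both arms, setting the effect to zero in those missing lowers the estimate by the missing fraction times the effect. For an effect at z = 1.96:
- 0.163 × 1.96 = 0.32 SE
- 0.20 × 1.96 = 0.39 SE

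This gap is about 2.5–2.8 times the Monte Carlo SE of a single estimate (0.32/0.128; 0.39/0.141). If the scenarios are imputed with separate draws (an assumption), the simulated seed-to-seed SD of the gap is 0.17–0.19 SE, about half the gap. At m = 100 it is 0.05–0.06 SE. Shared draws would reduce this noise.

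**The case against.** The strongest reply is that nothing here is wrong. Rubin's variance includes the (1 + 1/m) term, so tests and intervals at m = 10 are valid, with no bias and no type I error fault, and efficiency is 98%. The analyses are supportive, and no conclusion of the trial is made to depend on their p-values. All of this stands, and it is why the point is an optional improvement.

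The threshold-crossing figures also describe the unfavourable case. They matter only near p = 0.05, and having eight results does not make any of them likely to be borderline. At exactly 0.05 any finite number of imputations can fall either side, and the range at m = 100 still straddles the line. This stands too; the gain is a narrower band, not its removal.

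A reader might infer a larger FMI, such as 0.30, because the activity sensor must be worn for several days. The documents do not support that. The Sample size section anticipates 200 per group with follow-up data, and the section on objectively measured behaviours keeps participants who lack individual calibration by using a group equation. FMI could instead be lower for smoking, if baseline self-report enters the imputation model.

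A reader might also infer that the words about a recommendation are mistaken. That cannot be checked from the article, and on efficiency the choice is defensible. Nor is the absence of a stated seed or of a Monte Carlo error report a fault, since a condensed article leaves such detail to the full plan.

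What the reply does not answer is that the number is fixed in the text, and that it is coarse for comparing two scenarios a few tenths of a standard error apart.

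**Conclusion.** The point holds as a minor matter of reproducibility. At the planned loss, ten imputations leave seed noise of about 0.13–0.14 SE. A sensitivity p-value of 0.05 could be reported anywhere from about 0.02 to 0.11, and one of 0.03 or 0.07 would change sides of 0.05 in roughly one run in six to eleven. Clear results are hardly affected.

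This rests on FMI being about equal to the missing fraction, on 16–20% missing, and on a simulation with a continuous outcome. The √(FMI/m) formula is general, but the two binary outcomes were not simulated. It would be wrong to conclude that the sensitivity analyses are invalid or that the trial's main result is at risk: the primary intention-to-treat comparison does not use the imputed data.

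**What to change.** In the Statistical analysis section, replace ten with about 100 imputed datasets for each scenario. The Monte Carlo SE falls to about 0.04–0.045 SE, and the range around a p-value of 0.05 narrows to about 0.04–0.06. For 478 participants, four outcomes and two scenarios, the cost is a little computing time. No other part of the design or analysis changes.

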### Sample size

The trial was designed within the main *ADDITION-Cambridge *trial. It was anticipated that 500 patients would participate in the *ADDITION-Plus *trial and that 200 individuals per group would be available with follow-up data. With these numbers, there is 80% power at the 5% level of significance level to detect the following relevant differences between arms in primary outcomes:

Physical activity:

A 0.017 kJ/kg/min difference in PAEE. This is based on a standard deviation of 0.058 at baseline in the *ProActive *trial dataset [72] with mean 0.078. A 0.017 absolute difference represents a 22% relative difference in mean energy expenditure between groups.

Diet:

A 5.5 umol/l difference in plasma vitamin C (control group mean 53, SD 19, EPIC study [73]). Adjustment for baseline level in the analysis allows a finer difference of 4.0 umol/l to be detected between arms (EPIC test-rest correlation of 0.67).

Medication adherence:

A 10% absolute difference in the proportion of low adherers to hypoglycaemic medications (control group 18%, Supported Adherence to Medication pilot study [51]).

Smoking:

A 9.5% absolute difference in the proportion smoking (control group 17.9%).

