***Costs***				

Self-reported current medication/vitamins	X	X	X	X

Personal patient costs^1^	X	X		

Health service and medication use in the previous three months (adapted from the Aberdeen Health Service Research Unit questionnaire) ^1^			X	X

C = control group; I = intervention group; ^1 ^Questionnaire developed for the study

3. Treatment targets: HbA_1c _<7% (with a recommendation to initiate treatment at a threshold of 6.5%), blood pressure≤135/85 mmHg, total cholesterol <5 mmol/l or < 4.5 mmol/l for people with a history of ischaemic heart disease.

4. Audit and feedback: Interactive practice-based audit and feedback sessions were organised around 6 and 14 months after the academic detailing session and annually thereafter. They consisted of discussion of overall achievement of treatment targets and optimisation of the management of individual patients.

5. Provision of glucometers for patients: Blood glucometers and training in their use were provided to the primary care team. However, the decision to offer a glucometer to a patient was left to practitioners.

6. Theory-based diabetes education: Practice nurses were provided with theory-based education materials to discuss with, and give to patients in order to provide a shared framework for the causes, consequences and treatment of diabetes ('*Getting Started with Diabetes*'). The materials were developed by a multidisciplinary team and drew on Leventhal's Common-Sense Model [41]. They cross-referred to '*Diabetes for Beginners-Type 2' *a Diabetes UK publication [42] that was included in the patient information pack. The materials stressed the importance of a healthy lifestyle for the control of diabetes and associated health problems and provided targets for behaviour change. Specifically, participants with a BMI > 28 kg/m^2 ^were encouraged to lose 5-10% of their body weight, and all participants to increase physical activity gradually (recommendations to reach the equivalent of 35 minutes of brisk walking per day for 7 days per week), decrease the consumption of fatty foods and sugar, increase the consumption of fruit, vegetables, and whole grains, avoid excessive alcohol intake, take their medication regularly, self-monitor their blood glucose level (if applicable) and attend annual health checks. Participants who smoked were encouraged to stop.

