#### Objectively measured health behaviours

Physical activity was assessed at one-year using a combined heart rate and movement sensor (Actiheart, CamNtech, Cambridge, UK), which was worn continuously for at least 4 days [46]. A graded treadmill walk test was used for individual calibration of heart rate [47], a procedure which also provides an estimate of cardio-respiratory fitness by extrapolation of the HR-VO2 relationship to age-predicted maximal heart rate [48]. Heart rate data collected during the free-living period were pre-processed [49] and activity intensity (J/min/kg) was estimated using a branched equation framework [47,50]. Resulting time-series data were summarised into physical activity energy expenditure (PAEE, in kJ/kg/day) and time spent in sedentary and moderate-to-vigorous intensity physical activity (SPA and MVPA, min/day), whilst minimising diurnal information bias caused by non-wear periods (segments of non-physiological data). Participants without individual calibration data but who provided data during free-living were processed using an age, sex, beta blocker, and sleeping heart rate adjusted group calibration equation for the translation of heart rate into activity intensity.

Dietary intake was assessed at baseline and one-year by plasma vitamin C levels. Vitamin C is not endogenously produced and therefore provides a robust measurement of consumption. Medication adherence was assessed at one-year by plasma drug levels. Concentrations of metformin, simvastatin and atorvastatin in plasma samples were measured by liquid-chromatography mass-spectrometry (LC-MS/MS) after protein precipitation extraction. The LC-MS/MS methods for simvastatin and atorvastatin were established at Quotient Bioresearch Ltd. (Fordham) for the *ADDITION-Plus *study. The metformin method was validated at Quotient Bioresearch Ltd. (Fordham) for a previous study [51]. The calibration ranges for each of the analytes were as follows: metformin 5.00-5000 ng/mL, simvastatin 0.100-50.0 ng/mL and atorvastatin 0.0600 to 30.0 ng/mL. Objective measurement of smoking was assessed by analysis of cotinine levels in plasma samples using an Immulite^® ^Nicotine metabolite solid phase competitive chemiluminescent immunoassay (Siemens).

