#### Intervention evaluation

Participants in the intervention group completed 10 items at one year about their views on the frequency of contacts with the lifestyle facilitators, clarity of advice given, educational materials, and overall intervention. They also completed a skills questionnaire assessing their confidence in relation to using nine skills (e.g., goal setting, action planning, self-monitoring) on a 10-point scale ranging from 'not at all confident' to 'very confident', and use of these skills in the past 11 months in order to increase physical activity, eat a lower-fat diet, try to stop smoking (if applicable) and try to take medicines regularly as prescribed (if applicable) on a binary scale (yes/no).

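### The adherence power counts all 200 followed-up participants per arm, but the outcome is measurable only in those prescribed metformin; 80% holds only if about 177 of the 200 are

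*Protocol article*

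**What the plan says.** The Sample size section of the protocol article expects that "200 individuals per group would be available with follow-up data". It then says that, on these numbers, "there is 80% power at the 5% level of significance level to detect the following relevant differences between arms in primary outcomes". The adherence entry is "A 10% absolute difference in the proportion of low adherers to hypoglycaemic medications", with the control rate given as "control group 18%, Supported Adherence to Medication pilot study". No smaller denominator is given for this outcome.

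Other sections bear on who can contribute:

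- **Participants:** entry requires age 40 to 69 and type 2 diabetes, found by screening or diagnosed clinically in the preceding three years. Glucose-lowering treatment is not a condition of entry.
- **Design and setting:** 239 of the 478 randomised were screen-detected.
- **Intensive treatment (comparison arm), treatment targets:** the HbA1c target comes "with a recommendation to initiate treatment at a threshold of 6.5"%, so treatment is conditional on the HbA1c level.
- **Intensive treatment (comparison arm), treatment algorithms:** the choice of individual drug is left to GPs and patients.
- **Objectively measured health behaviours:** "Concentrations of metformin, simvastatin and atorvastatin in plasma samples were measured" at one year. Metformin is the only glucose-lowering drug of the three.

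**The concern.** Low adherence to a drug is defined only for someone prescribed it, and it can be measured objectively here only if the drug is assayed. A participant on diet alone, or on a glucose-lowering drug other than metformin, gives no plasma measure of hypoglycaemic adherence. The power statement makes no allowance for such participants. The 200 per group allows for loss to follow-up (500 anticipated, 400 with data) and for nothing else.

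Medication adherence is one of four primary outcomes. If the analysable group is clearly smaller than 200 per arm, a null result read against a stated 80% power for 10 points would look like better evidence of no effect than it is.

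**Working it through.** **Inputs from the Sample size section:** n = 200 per arm, p1 = 0.18, difference 0.10, so p2 = 0.08; power 80%, 5% level. **Taken by assumption:** a two-sided test, and 18% as a rate among people prescribed the drug.

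**Step 1: reproduce the plan's figure.** Pooled-variance formula for two proportions:

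n = [1.96·√(2·p̄·(1−p̄)) + 0.8416·√(p1(1−p1) + p2(1−p2))]² / d²

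With p̄ = 0.13: √(2·0.13·0.87) = √0.2262 = 0.4756, and √(0.1476 + 0.0736) = √0.2212 = 0.4703.

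n = (0.9322 + 0.3958)² / 0.01 = 176.4, so 177 per arm.

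With continuity correction, n' = (n/4)·[1 + √(1 + 4/(n·d))]² = 44.1 × (1 + 1.1076)² = 195.9, so 196 per arm.

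Power at 200 per arm = Φ[(0.10·√200 − 0.9322)/0.4703] = Φ(1.025) = 84.7%; with continuity correction, 80.9%. The stated claim therefore reproduces on the full 200. Read as a rise to 28% it would not: that needs 277 per arm.

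**Step 2: break-even share.** 177/200 = 88.5% must be measurable to keep 80%, or 196/200 = 98% with continuity correction. The neighbouring smoking line (17.9%, 9.5 points) needs 198 per arm uncorrected, while the corrected formula would put its detectable difference at about 9.9 points. The uncorrected formula is therefore the likelier source, and 177 is the fairer break-even.

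**Step 3: power on the measurable subset.** The share f prescribed metformin at one year is not in the document, so every f below is an assumption. The detectable difference is the d that solves the Step 1 formula for n = 200f with p1 = 0.18.

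| f | n per arm | Power, 18% v 8% | With continuity correction | Detectable at 80% power (uncorrected) |
|---|---|---|---|---|
| 1.0 | 200 | 84.7% | 80.9% | 9.5 points |
| 0.9 | 180 | 80.8% | 76.2% | 9.9 points |
| 0.8 | 160 | 76.0% | 70.5% | 10.4 points |
| 0.7 | 140 | 70.3% | 63.8% | 11.0 points |
| 0.5 | 100 | 55.7% | 47.3% | 12.6 points |

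**Step 4: does keeping everyone in the denominator help?** Suppose those without the drug are counted as not low adherers. The comparison becomes 18f% v 8f% on 200 per arm. Power is 74.7%, 68.3% and 52.7% at f = 0.8, 0.7 and 0.5, slightly worse than the subset analysis.

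**Step 5: does fuller follow-up help?** If all 239 randomised per arm were followed up, the break-even share would be 177/239 = 74%. Power would be 83.1%, 77.9% and 63.4% at f = 0.8, 0.7 and 0.5. This eases the problem but does not remove it.

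**The case against.** Three stronger readings are tempting, and the document supports none of them.

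- **That the 80% power is missed.** A reader might infer this from the mismatch alone. But a denominator below 200 is not necessarily below 177. The uncorrected calculation tolerates about 11% of participants without a measurable drug, and the metformin share is not reported.
- **That the arithmetic is wrong.** It is not: the figure reproduces on its stated inputs. The weakness is the denominator.
- **That metformin is the only drug assayed, so the adherence outcome as a whole is underpowered.** Two statins are assayed as well, and the primary outcome is described as medication adherence by plasma drug levels. However, the power line is confined to hypoglycaemic medications, so the statins add nothing to that line.

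The other side has further fair points. Adherence is measured after a year of intensive, target-led care with a threshold below the HbA1c target, so metformin use at one year could be well above its level at entry. The skills questionnaire, which treats medicine-taking as not applicable to everyone, goes only to the intervention group and concerns medicines in general, so it says little about the metformin share. The article is also condensed, and a prescribing assumption may stand in the full protocol.

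These points limit how large a shortfall can be claimed. They do not answer the mismatch, because the article states its base explicitly and its own eligibility, treatment and assay sections describe a smaller one.

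**Conclusion.** The point holds in conditional form. The adherence power rests on all 200 followed-up participants per arm, while the measurable outcome exists only in those prescribed metformin. The stated 80% needs at least about 177 of 200 per arm (88.5%) on that one drug at one year, or 196 with continuity correction. Nothing in the document supports a share that high in a cohort that is half screen-detected, treated from a threshold, and free to use other drugs.

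The size of any shortfall is an assumption. It is modest at a share of 80% (power about 76%) and serious at 50% (about 56%). The conclusion assumes a two-sided test, a fall from 18% to 8%, and 18% as the rate among people prescribed the drug.

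**What to change.** In the Sample size section, restate the adherence power and the difference detectable with 80% power on the number expected to be prescribed metformin at one year. Baseline medication records (Table 1) can guide that number. Since they need not match prescribing a year later, give a range of shares and not a single value.

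State that this outcome is assessed in the subset prescribed the assayed drug. Report the number prescribed each of the three assayed drugs by arm, because prescribing at one year arises after randomisation and could differ between groups. Self-reported current medication is already collected at both time points.

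The cost is rewording and, very probably, a less favourable stated power. No new data are needed.

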### Trial analysis

1. Can a facilitator-led intervention, based on theory and evidence from psychology, to increase and maintain health-promoting behaviours (physical activity, dietary change, taking medication and smoking cessation) achieve clinically important and measurable change in these behaviours when offered to people with screen-detected diabetes and to those recently diagnosed with diabetes?

Primary outcomes include *objectively measured *physical activity, fruit and vegetable intake, medication adherence, and smoking status.

Secondary outcomes include (i) a composite measure of behaviour derived from the four primary outcomes; (ii) self-reported behaviours; (iii) modelled cardiovascular risk (UKPDS risk engine, v3[33]); (iv) levels of individual clinical risk factors; (v) functional status, health utility and quality of life; and (vi) costs and cost-effectiveness.

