### Participants

Eligibility criteria (initially assessed by general practice staff) included: age (40-69yrs) with type 2 diabetes following (i) screening in the *ADDITION *programme or (ii) clinical diagnosis during the three previous years in participating GP surgeries. Exclusion criteria included women who were pregnant or lactating or anybody who had a psychotic illness or an illness with a likely prognosis of less than one year.

Individual randomisation of participants to one of two carefully characterised interventions was independent of intervention facilitators, study coordination and measurement teams, and central using a partial minimisation procedure that dynamically adjusted the randomisation probabilities to balance stratifiers (age, sex and general practice, and within screen-detected and clinically-diagnosed subgroups: smoking, self-reported medication adherence [34] and BMI). The stratifiers were individually weighted in order that those with more categories (such as general practice) could achieve an even distribution between the two arms. A random element was included in the minimisation to allow a sound basis for inference.

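### The primary smoking test ignores baseline smoking status, so it has little power for cessation and does not estimate it

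*Protocol article*

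**What the plan says.** - **Question.** Research question 1 (Protocol article, Trial analysis) asks about change in four behaviours: "physical activity, dietary change, taking medication and smoking cessation". Objectively measured smoking status is one of the four primary outcomes.
- **Population.** Eligibility (Participants) rests on age and type 2 diabetes; smoking is not required. Smoking is a minimisation factor within the two diagnosis-route subgroups, listed as "smoking, self-reported medication adherence [34] and BMI".
- **Power.** Sample size expects that "200 individuals per group would be available with follow-up data" and states that "there is 80% power at the 5% level of significance level". For smoking, the difference to detect is "A 9.5% absolute difference in the proportion smoking (control group 17.9" (per cent).
- **Test.** Statistical analysis gives "a comparison of proportions for binary outcomes", by intention to treat. Adjustment for baseline is described for continuous outcomes only. Adjustment for stratifiers is excluded. Subgroup analyses are confined to route of diagnosis.
- **Measurement.** In Table 1, plasma cotinine is taken at one year only. Questionnaire smoking status is taken at baseline and at one year.
- **A phrase that points the other way.** The same analysis section speaks of "change from baseline in plasma vitamin C and smoking status". It does not say how a change in smoking status would be formed, and it does not restrict the analysis to smokers.

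**The concern.** Cessation is open only to people who smoke. The protocol accepts this elsewhere: its advice to stop is aimed at smokers, and the skills questionnaire asks about stopping only where it applies. Yet the primary test takes every participant as denominator and, as written, makes no use of who smoked at the start. Non-smokers then add sampling variation to the comparison but carry no information on quitting.

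Two things are at stake. First, the test detects only a very large effect among smokers, which is hidden when the target is given as 9.5 points over everyone and called relevant. Second, the estimate is a difference in smoking prevalence, not a cessation effect. The Discussion says that the results will inform policy on health trainers, so a null prevalence comparison could be misread as evidence against an effect on cessation.

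**Working it through.** **Inputs from the protocol article.** Control proportion smoking 0.179; difference 0.095, so 0.084 under the intervention; 200 per group; 5% level, taken as two-sided because sidedness is not stated; 1:1 allocation (the abstract gives "intensive treatment alone (n = 239" and the same number in the other arm).

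**1. The plan's own figure.** Power = Φ[(d − 1.96·SE₀)/SE₁], with SE₀ from the pooled proportion and SE₁ from the separate proportions.
- Pooled proportion = (0.179 + 0.084)/2 = 0.1315; SE₀ = √(2 × 0.1315 × 0.8685/200) = 0.0338.
- SE₁ = √(0.179 × 0.821/200 + 0.084 × 0.916/200) = 0.0335.
- Power = Φ[(0.095 − 1.96 × 0.0338)/0.0335] = 80.5%; the required n is 198 per group.

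The stated power is reproduced, with all 200 per group as denominator.

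**2. What 9.5 points means among smokers.**
- Non-smokers in the planned control group: 100 − 17.9 = 82.1%.
- Smokers at follow-up per 200: 35.8 under control (0.179 × 200) and 16.8 under the intervention (0.084 × 200).
- Share of those who would still smoke under control who must stop: 0.095/0.179 = 53.1%.

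To express this as a quit-rate difference, the control quit rate q is needed. The article does not give it, so a range is assumed, with no uptake among non-smokers. Baseline prevalence is then b = 0.179/(1 − q), and the difference required is 0.095/b.

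| Assumed q | Baseline smokers per arm (200b) | Quit-rate gain required |
|---|---|---|
| 5% | 38 | 50 points |
| 10% | 40 | 48 points |
| 15% | 42 | 45 points |
| 20% | 45 | 42 points |

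**3. Power for smaller effects.** Assume quit rates of 10% and 25%. Then b = 0.179/0.9 = 0.199, or 39.8 smokers per arm. Power is Φ(z − 1.96), with z from the separate proportions.
- All participants: 0.179 v 0.199 × 0.75 = 0.149; difference 0.030; SE = √(0.179 × 0.821/200 + 0.149 × 0.851/200) = 0.037; z = 0.81; power about 12%.
- Baseline smokers: difference 0.15; SE = √(0.10 × 0.90/39.8 + 0.25 × 0.75/39.8) = 0.0835; z = 1.80; power about 43%.

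The same formulas for 10% v 40% give 39% and 91%. For a 15-point gain across q = 5% to 20%, the ranges are 12–15% for all participants and 36–52% for baseline smokers.

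**4. Keeping everyone but stratifying by baseline smoking.** With no uptake, non-smokers contribute neither difference nor variance. The stratified difference is 0.199 × 0.15 = 0.0298, with SE 0.199 × 0.0835 = 0.0166. This gives z = 1.80, as among smokers alone.

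If instead 1% of recorded non-smokers in each arm are cotinine-positive at one year (n = 200 − 39.8 = 160.2, weight 0.801), the added variance is 0.801² × 2 × 0.01 × 0.99/160.2 = 0.000079. The SE becomes √(0.0166² + 0.000079) = 0.0188, z is 0.0298/0.0188 = 1.58, and power is about 35%. Most of the gain over the crude test remains.

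**The case against.** The strongest reply is that the whole-sample comparison is a legitimate estimand. The primary outcome is smoking status, the intervention was offered to everyone randomised, and prevalence by arm is an unbiased intention-to-treat effect that also captures relapse and uptake. That stands: the fault is not bias, and dropping non-smokers altogether would lose something.

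Further points that stand:
- Baseline smokers can be identified only by self-report, which the Background itself calls imprecise. A smokers-only primary analysis would let self-report define the set for an outcome meant to be objective.
- About 40 smokers per arm is few. By the same calculations, 80% power among smokers still needs a gain of about 24 to 28 points.

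Stronger readings that a reader might infer, and that the document does not support:
- *That over half of all baseline smokers must quit beyond control.* The 53% is a share of those who would still smoke under control. A gain above 50 points needs a control quit rate below about 5.8% (1 − 0.5 × 0.179/0.095), and no such rate is given.
- *That dilution weakens the evidence about five-fold.* The absolute difference shrinks five-fold, but so does much of the variance. In the example z falls from 1.80 to 0.81, about 2.2-fold, and the relative risk of still smoking is unchanged (0.149/0.179 = 0.75/0.90 = 0.83).
- *That a null will be reported as no effect on cessation.* No passage commits to that.

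It may also be said that "change from baseline in plasma vitamin C and smoking status" gives baseline status a role, with the details left to a fuller document. The phrase is ambiguous, but it does not remove the point. Cotinine has no baseline value, the power statement uses the plain proportion in everyone, and the article goes beyond silence: it limits baseline adjustment to continuous outcomes and excludes stratifier adjustment.

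**Conclusion.** The point holds as one of precision and interpretation. The sample-size arithmetic is correct and the randomised comparison is valid. But the plan tests a cessation question with a crude prevalence difference that leaves out a strong, already recorded baseline predictor. The target of 9.5 points corresponds to 53% of those who would still smoke under control stopping, or a quit-rate gain of about 42 to 50 points at assumed control quit rates of 20% down to 5%. At an assumed 10% v 25%, power is about 12% in the crude test against about 43% among baseline smokers.

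The 53% follows from the article's figures alone. The quit-rate and power comparisons rest on assumed quit rates, no uptake among non-smokers, 200 followed up per arm, and a normal approximation that is rough at about 40 per arm. Across the range examined, using baseline smoking improved power for every effect considered, though it did not bring modest effects to 80%.

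**What to change.** Use baseline smoking status in the primary smoking analysis, in one of two ways:
1. keep all participants and stratify or adjust the comparison by baseline smoking; or
2. estimate cotinine-defined non-smoking at one year among baseline smokers, by randomised arm.

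In either case, prespecify the baseline-smoker estimate and report it with its confidence interval beside the whole-sample proportion. In Sample size, state that 9.5 points equals 53% of those who would still smoke under control. In Statistical analysis, make an exception for this outcome to the rules on baseline and stratifier adjustment, and say what change from baseline in smoking status means when cotinine is measured only at one year. State that a null whole-sample result will not be read as evidence of no effect on cessation.

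**Cost.** No new data are needed: smoking is recorded before randomisation and is a minimisation factor, so the randomised comparison is preserved. Baseline classification is by self-report, the smoker estimate rests on about 40 people per arm and will be imprecise, and under the second option relapse and uptake are seen only in the whole-sample analysis. The first option excludes nobody and, on the check above, keeps most of the gain in power.
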